Functional and frailty tests	X					X		X
CRT diary (report on training days and performance)			X	X	X	X	X	X
Left of tablets count of drugs						X		X
Adherence to MedD	X					X		X
Food diary – 3 days			X			X		X
Quality of life	X					X		X
Phone calls (adverse events monitoring)			X	X	X	X	X	X
Encouragement using phone calls			X	X	X	X	X	X

^a^Allocation concealment until the end of baseline day – then allocation is introduced both to researcher and the subjects. Subjects allocated to SGLT-2 would meet physician at the end of the day for instruction of the use of the drug and will be supplied with drugs for 20 weeks). Subjects allocated to Diet and CRT groups will make an appointment for the following week (familiarization)

^b^For diet subjects – on site visit and for CRT subjects – familiarization at their homes

^c^At this week CRT group will finish the study and SGLTT-2 and V-Med add CRT on top of their current intervention. Familiarization of the CRT will be performed on the same week.

*Abbreviations*: *BIA* Bioelectrical Impedance Analysis, *BMI* Body Mass Index, *CRT* Circuit Resistance Training, *HbA1c* Hemoglobin A1C, *MedD* Mediterranean Diet

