Primary analysis will be intent to treat analysis. It will include all patients that had been randomized, started protocol and reached the end of the trial examinations (or last observation available will be imputed as their “end of study value”). Per protocol analysis will be performed by the a-priori conditions: a) for participants who had high compliance to workout (≥ 2/3 of sessions); b) for participants who had high compliance to diet (≥ score 9 in the Med-diet score and/or caloric consumption change from baseline was not more than 15% of report at baseline); c) for participants who had high compliance to drug therapy (≥80% tablets taken); d) for participants who did not violate the protocol (for example: changed thier habitual diet in the CRT arm; initiated new physical activity other than the one prescrived by us, ect.).

Sensitivity analysis can include all the participants who finished the trial including dropouts, with imputation of the last observation. This will be compared to an analysis which includes only participants that fully completed the study (have an assessment at the end of study).

We may also perform a mixed model for repeated measurements based on assessments of participants who completed the study and had high compliance to the treatment. An unstructured covariance matrix for measurements within the same participant will be employed, assuming that measurements for different participants are independent. The covariates and factors in Table 2 will be nested in the model.

Last, subgroup analysis will be done by stratification to several factors shown in Table 2, where ANCOVA or logistic regression models will be performed according to the outcome assessed (Table 3).

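### The set labelled intent to treat omits randomised non-starters, and last observation carried forward fills week 10 with baseline values and week 20 with pre-CRT values

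*Protocol article*

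**What the plan says.** All the analysis rules stand in the protocol article, Statistical methods, under Baseline comparisons.

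- **Label:** "Primary analysis will be intent to treat analysis".
- **Set:** "It will include all patients that had been randomized, started protocol and reached the end of the trial examinations". A parenthesis adds a route for those without a final examination: "or last observation available will be imputed as their" end-of-study value.
- **Sensitivity analysis:** "Sensitivity analysis can include all the participants who finished the trial including dropouts, with imputation of the last observation". This is to be compared with "an analysis which includes only participants that fully completed the study".
- **Optional further model:** a "mixed model for repeated measurements based on assessments of participants who completed the study and had high compliance to the treatment", with an unstructured covariance matrix.

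Table 1 schedules body weight and bioimpedance measures (fat, lean and muscle mass) at baseline, week 10 and week 20 only. Footnote c of that table says: "At this week CRT group will finish the study and SGLTT-2 and V-Med add CRT on top of their current intervention". Table 3 lists percentage change in weight, change in percentage lean mass and the proportion losing at least 2.5% as primary outcomes, at weeks 10 and 20.

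**The concern.** An intention-to-treat analysis keeps everyone randomised in the arm assigned. This one requires that the participant started. Footnote a of Table 1 shows why that could matter. Allocation is disclosed at the end of the baseline day. Drug-arm participants are instructed and supplied the same day, while diet and CRT participants book an appointment for the following week. The chance of not starting after learning the allocation can therefore differ by arm, in an open-label trial.

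The imputation rule is the second problem. Last observation carried forward (LOCF) can only use a value that exists, and the visit schedule offers either the baseline value or a week-10 value that precedes the combination phase. Neither carries information about the quantity it replaces. At stake are the primary estimates at both time points, above all at week 20, where Hypotheses 1 and 2 compare diet plus CRT with drug plus CRT.

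**Working it through.** **Inputs.** From the Sample size section: difference -3.2 kg at week 10 (drug against CRT), no weight change with CRT alone, 80% power, 5% significance, 40 per arm, attrition about 10%, recruitment of 120 up to 140. Two-sided testing is assumed. No SD for weight is stated.

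**1. Reproducing the planned size.** SD = 3.2 × √(40/2) / (1.960 + 0.842) = 5.11 kg by the normal approximation, or 5.04 kg by the t-test. About 5.05 kg is used below, as an assumption. The second calculation in that section (body fat 37, 36 and 40%, SD 6%) gives f = 0.283, hence 41 per arm for 80% power and 78.9% power at 40. The stated 40 per arm is reproduced closely enough.

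**2. What LOCF has available to carry**

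| Dropout occurs | Last value | Analysed as |
|---|---|---|
| Before week 10, any arm | Baseline | Week-10 change of 0 |
| Before week 10, diet or drug | Baseline | Week-20 combination change of 0 |
| Weeks 10 to 20, diet or drug | Week 10, before CRT | Week-20 combination result |

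For the outcome of at least 2.5% weight loss, a change of zero is a non-response by construction. With dropout d, the analysed response proportion is (1 - d) times the proportion among those measured.

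**3. Week-10 estimate.** If dropouts would have had their arm's mean effect, the expected LOCF difference is μ(drug) × (1 - d(drug)) - μ(CRT) × (1 - d(CRT)). With μ(CRT) = 0:

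- d(drug) = 10%: -3.2 × 0.90 = -2.88 kg
- d(drug) = 15%: -3.2 × 0.85 = -2.72 kg
- d(drug) = 20%: -3.2 × 0.80 = -2.56 kg

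If dropouts would have had only a fraction k of the effect, and those measured average -3.2 kg, the attenuation is 3.2 × k × d. At d = 10% that is 0.32 kg for k = 1, 0.16 kg for k = 0.5 and none for k = 0. A negative k reverses the sign.

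**4. Week-10 power.** 20,000 simulated trials per row, SD 5.05 kg, two-sample t-test on change in kg, random dropout:

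| Per arm | Dropout drug / CRT | LOCF estimate | LOCF power | Observed-data power |
|---|---|---|---|---|
| 40 | 10% / 10% | -2.88 kg | 74.6% | 75.1% |
| 40 | 15% / 5% | -2.72 kg | 70% | 75% |
| 40 | 20% / 10% | -2.55 kg | 67% | 73% |
| 46 | 10% / 10% | about -2.88 kg | 80.4% | 81.0% |

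Observed data give about -3.2 kg throughout, because dropout here is random. With no true change in either arm, the LOCF type I error is about 5%.

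**5. Week 20.** Let g be the true change from week 10 to week 20 in an arm, and p the proportion lost in that interval. LOCF removes p × g from that arm's mean. If g is the same in both arms, the diet-minus-drug contrast acquires a false component g × (p(drug) - p(diet)). With p = 20% and 10%, that is 0.1 × g, or 0.1 to 0.2 units for g of 1 to 2 units. If p is equal but g differs, the CRT-phase contrast shrinks by the proportion p. The documents give no value of g, so these are illustrations.

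**6. What the other analyses cover.** The sensitivity comparison sets LOCF against completers. The mixed model is "based on assessments of participants who completed the study and had high compliance to the treatment", which selects on two events after randomisation. No planned analysis keeps all randomised participants under a principled missing-data assumption.

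**The case against.** Several stronger readings are tempting and are not supported.

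- *The primary set is completers only.* The parenthesis retains started dropouts by imputation. Only non-starters are clearly excluded.
- *LOCF takes power from 80% to about 75% at the planned attrition.* Observed data lose the same amount, so the fall is lost sample size. Recruitment may reach 140, and about 46 per arm restores power to about 80% or 81%. A distinct LOCF cost appears only with unequal dropout, for which the documents give no figures.
- *The imputed zeros invalidate the test.* At week 10, under no change in either arm and random dropout, type I error stays at about 5%. This does not extend to week 20 or to informative dropout.
- *The sensitivity analysis tests nothing new.* LOCF and completers are two different missing-data assumptions, so the comparison has some value.
- *The bias has a known direction.* It does not. Under the plan's zero-change assumption, the CRT arm's mean weight change is unaffected by carrying baseline forward. The lean-mass gain expected under Hypothesis 1 would be diluted. Week 20 can move either way.

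It is also fair to say that the trial is described as exploratory, that attrition is expected to be modest, and that the figures above use change in kg and a t-test while the primary endpoint is percentage change by ANCOVA. These points limit the week-10 size. They do not answer the week-20 problem or the label.

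**Conclusion.** The concern stands. The primary set does not match its intent-to-treat label, and LOCF with this visit schedule supplies uninformative values at both primary time points. Week 20 is the most serious, because pre-CRT measurements are counted as combination results. Its size cannot be fixed from the documents.

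At week 10 the planned -3.2 kg becomes about -2.9 kg at 10% dropout, and about -2.55 kg at 20% drug and 10% CRT dropout. These figures rest on a back-calculated SD (which affects the power figures only), on zero weight change with CRT, and on dropouts otherwise having their arm's mean effect. The defect is one of estimation and labelling. At equal 10% dropout it is not a loss of power. The rules are written into the protocol article, so this is not a detail left to an unseen analysis plan.

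**What to change.** - Define the primary set as all randomised participants, analysed in the arm assigned, whether or not they started.
- Make the unstructured mixed model primary for the continuous endpoints. Use all observed baseline, week-10 and week-20 values (week 20 for the diet and drug arms), with baseline value and gender in the model.
- Remove the restriction to compliant completers, and drop LOCF as the primary rule.
- State a missing-data rule for the 2.5% responder outcome that fits the same assumption.
- Add a sensitivity analysis covering all randomised participants that departs from missing at random, for example multiple imputation with a shift for dropouts. Other choices would serve. LOCF and completer analyses can stay as supportive at most.

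The cost is revised wording and modest programming, with no new data or visits. The primary result would then rely on missing at random, which the added sensitivity analysis examines. At week 10 a participant lost early has no post-baseline value, so the mixed model is close to a baseline-adjusted ANCOVA of observed cases, and the main gain there is removing the imputed zeros. At week 20 it gains more, by using the week-10 values of those lost later without treating them as week-20 outcomes.

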## Abstract

**Background:**

Treatment of the older diabetic individual comprises a therapeutic challenge. Currently little scientific evidence exists depicting the best approach to type 2 diabetes treatment in this growing sub-population of patients. The purpose of this study is to assess the effects of a modified plant-based Mediterranean diet (“vegeterranean” diet), circuit resistance training (CRT) and empagliflozin, separately or in combination, on body composition and physical function in older subjects with type 2 diabetes. The rationale for this study is to assess three interventions associated with a negative energy/caloric balance (increased caloric use in exercise, caloric restriction in the “vegeterranean” diet and caloric wasting by glycosuria with empagliflozin), their interaction and effect on body composition and physical function.

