#### “Vegeterranean” diet (V-med diet)

Briefly, the Med-diet is rich in olive oil, legumes, fish, chicken, nuts, milk products, fruits & vegetable. The modified V-Med diet in the study will be considered as ad-libitum (using fat sources) aimed for a minimum of 1 g/kg/day of protein, limiting carbohydrates: 3 servings for men and 2 servings for women per main meal and 1 serving per intermediate meal for both genders (medium/low glycemic index carbohydrates will be recommended). Subjects will be encouraged to consume ≥25 g of dietary fibers [37]. Subjects will be asked to avoid red meat and poultry completely and the consumption of dairy and eggs products will be limited to 2 servings per day. Three servings of fish should be consumed during the week. Legumes will comprise the source of the residual protein consumption, by the study’s team recommendations. The target legume consumption will be 0.75–1.5 cup per day (1–2 servings per day) of cooked beans, chickpeas or lentils and/or using pulses-based flour or pulses-based bread. Other sources for fibers will be recommended by consumption of whole grain carbohydrate foods (preferably millet, groats, bulgur, red-rice or “pseudo grains” like quinoa, buckwheat). Participants will be provided with a checklist of 15-g carbohydrate portions and of 10-g protein portions of recommended foods and the quantities they were expected to consume daily (as previously shown in [38]).

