#### Measures of compliance/adherence

Compliance would be monitored in all three arms. Subject’s adherence to the exercise regimen will be assessed based on subject reporting and documentation in a dedicated booklet. Good compliance/adherence would be considered as performing ≥2/3 of original workout plan. Adherence to the V-Med diet will be based on a questionnaire scoring the diet implementation [39]. A score < 9 would be considered as low adherence, and ≥ 9 as high adherence. Adherence to the diet will also be assessed from 3-day food records or at least from 24 h recall report at the weeks 10 and 20 (visits 6, 9, respectively). For the drug arm, a recall of unused tablets would be performed after 10 weeks and at the end of the study. Consumption of less than 80% of study medication would be considered poor adherence to therapy.

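### The per-protocol rule for diet compliance joins a diet score and a calorie limit by and/or, and on either reading it contradicts the adherence rule in the compliance section

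*Protocol article*

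**What the plan says.** Two places in the Protocol article define adherence to the V-Med diet.

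- **Measures of compliance/adherence.** The instrument is a questionnaire: "Adherence to the V-Med diet will be based on a questionnaire scoring the diet implementation". The cut-off follows: "A score < 9 would be considered as low adherence, and ≥ 9 as high adherence". Food intake is a further source, with no threshold attached: "Adherence to the diet will also be assessed from 3-day food records or at least from 24 h recall report".
- **Statistical methods, Analysis (per-protocol paragraph after Table 3).** Condition b, presented as set in advance, selects analysis "for participants who had high compliance to diet". It is met by a minimum of "score 9 in the Med-diet score and/or caloric consumption change from baseline was not more than 15% of report at baseline".

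Two other places bear on what the calorie clause can mean.

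- The section on the V-Med diet sets no calorie target: "The modified V-Med diet in the study will be considered as ad-libitum". It describes the diet through foods, for example: "Subjects will be asked to avoid red meat and poultry completely".
- The Background of the Abstract gives negative energy balance as the common rationale of the three interventions. For exercise and diet the terms are "increased caloric use in exercise, caloric restriction in the" V-Med diet.

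**The concern.** A per-protocol analysis is meant to describe participants who followed the assigned intervention. Stable calorie intake is not evidence that an ad-libitum diet defined by food choice was adopted. It is also what someone who ignored the dietary advice would be expected to report. If stable intake alone is enough, people whom the compliance section labels low adherers are analysed as high compliers.

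If both parts are required, the rule instead removes people who scored as adherent but whose intake changed. Reduced intake is a stated route of action of the diet, and body weight is a primary outcome in Table 3, so this would be selection on a variable that lies between treatment and outcome.

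A rule joined by *and/or* also leaves open which set is meant. In a trial whose investigators are unblinded, that choice should not remain to be made once data are visible.

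**Working it through.** The plan gives no figure to reproduce. The check compares two logical rules, followed by an illustration on assumed inputs.

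**1. The two rules side by side.** The calorie change is read as two-sided, since the text gives it no sign.

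| Score ≥ 9 | Calories within 15% | Compliance section | Condition b as *or* | Condition b as *and* |
|---|---|---|---|---|
| yes | yes | high | high | high |
| yes | no | high | high | **not high** |
| no | yes | low | **high** | not high |
| no | no | low | not high | not high |

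Each reading departs from the compliance section in one of four cells, so neither reconciles the two passages. *And/or* is ordinarily an inclusive *or*, which makes the third row the more natural consequence. With the calorie clause deleted, the rules agree in all four cells.

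**2. How easily the calorie clause is met without adopting the diet (illustration).** Assume that the reported percentage change in calories is normal with mean 0 in a non-adopter. Its SD is not in the documents and is assumed. P(within 15%) = 2Φ(15/SD) − 1:

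| SD (percentage points) | 10 | 15 | 20 | 25 | 30 | 40 |
|---|---|---|---|---|---|---|
| Non-adopter passes on calories alone | 87% | 68% | 55% | 45% | 38% | 29% |

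**3. Make-up of the set under *or* (illustration).** Take the planned 40 per arm. Assume that 20% to 40% score below 9 and that half of these report intake within 15%, a value inside the range in step 2.

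- 20% low: 8 low scorers, 4 admitted, 32 high scorers; 4/(32 + 4) = 11% of the set.
- 40% low: 16 low scorers, 8 admitted, 24 high scorers; 8/(24 + 8) = 25% of the set.

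These shares describe who is in the set. They are not estimates of bias.

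**4. Who is lost under *and* (illustration).** With the same SDs, a participant with a score of 9 or more is dropped with probability 1 − P(within 15%).

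- Mean change 0: from 1 − 0.866 = 13% (SD 10) to 1 − 0.292 = 71% (SD 40).
- Mean change −20%: from 1 − 0.361 = 64% (SD 20) to 1 − 0.259 = 74% (SD 40).

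**The case against.** **The conflict may be softer than it looks.** The compliance section announces food records as a further source, so an intake criterion is foreshadowed. Condition d, on protocol violations, is an open list and could be used to exclude someone who ignored the diet. Neither point resolves the conflict. The food-record sentence sets no threshold and does not override the score cut-off. The examples under condition d do not include failure to adopt the diet.

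**The *and* reading is defensible in part.** For an ad-libitum diet in older people, a good score with stable intake could serve as a fidelity check. The main Background section also calls for careful management of weight reduction in the presence of anabolic resistance. This stands: the calorie-restriction rationale and the ad-libitum description pull in different directions, so the documents do not prove *and* to be senseless. It still contradicts the compliance section.

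**The score has its own limit.** It is called a Med-diet score, it is also taken at screening, and the listed eligibility criteria set no upper bound on it. Someone could enter with 9 or more, change nothing and still count as compliant. This stands too. A score-only rule restores consistency and closes the calorie-only route, but it does not prove adoption.

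**Stronger inferences that the documents do not support.**

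- *That the rule biases towards no diet effect by a known share.* All comparators are active. The sample-size section assumes no weight change under CRT and a loss of about 3–3.5 kg under empagliflozin. If the diet effect on weight lies between these, diluting it narrows the contrast with CRT and widens the contrast with empagliflozin. Hypothesis 1 concerns lean mass, where the direction is less clear still.
- *That the 15% limit belongs to the CRT and empagliflozin arms under condition d.* That condition names a change of habitual diet in the CRT arm only and gives no percentage. The main Background section expects compensatory hyperphagia with both exercise and SGLT2 inhibition, so such a limit would select on a treatment effect.
- *That the mixed model uses condition b.* It is optional and refers to high compliance without citing that condition.

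**Conclusion.** The contradiction holds on either reading of *and/or* and rests on the text alone. That a low scorer with unchanged intake becomes a high complier needs the *or* reading, which is the ordinary one. That a high scorer with changed intake is dropped needs the *and* reading.

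The reach is limited. The primary analysis is intent to treat and the trial is described as exploratory. What is affected is the per-protocol analysis, and possibly the optional mixed model in compliant completers. The proportions of 11% and 25% rest on assumed adherence rates and show only how the set could be composed. The direction and size of any bias in a treatment contrast cannot be determined from the documents.

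The point should be corrected before analysis, because the rule is stated as fixed in advance and yet yields two different sets.

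**What to change.** In condition b, define per-protocol diet compliance as a diet score of 9 or more at week 10, and at week 20 for week-20 analyses, in line with the compliance section. Delete the calorie clause from that condition. Do not transfer the 15% limit to the CRT or empagliflozin arms, where intake may change because of treatment.

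No new data are needed: Table 1 already schedules the diet-adherence score at screening, week 10 and week 20. Reporting the screening score next to the follow-up score would show how many participants already met the cut-off at entry.

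The cost is one sentence and a smaller per-protocol set than under *or*: 32 instead of 36, or 24 instead of 32, in the two illustrative cases. Compared with the *and* reading, the set would be the same size or larger.

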### Follow up visits

Subjects will attend the IEMH at TASMC at the following intervals: screening Visit 1, Visit 2- Day 1- baseline day (allocation will be exposed at the end of baseline day; subjects allocated to SGLT-2 arm will meet the physician (RE) for instructions on the drug), Visit 3 Week 0- familiarization of protocol – meeting with the dietitian (AB) for V-Med arm only. Subjects allocated to the CRT arm will meet the physiologist (OK) or a physical instructor (AR) at their homes for familiarization. From familiarization day the 20-week count of the study period will start, and subjects will have an additional five “on site visits” at Week 1 (V-Med arm only; CRT – another visit at home after 1 week from beginning), Week 6 (V-Med arm only), Week 10 (all arms; CRT arm – end of study), Week 16 (V-Med arm only) and Week 20 (SGLTT-2 and V-Med arms) (Table 1).

**Table 1 Tab1:** Study flow chart

	Screening	Baseline day (W0–1)^e^	Familiarization of protocol^b^ (W0–2)	After 1 week (W1)	After 6 weeks (W6)	After 10 weeks^c^ (W10)	After 16 weeks (W16)	After 20 weeks (W20)
On site visit number	1	2	3	4	5	6	7	8
Informed consent	X							
Eligibility criteria form	X							
Medical discharge and list of drugs from primary physician + physical activity confirmation letter	X							
Blood examinations from last 3 months (for eligibility)	X							
Physical examination for vital signs by study physician	X					X		X
Screening blood and urine tests (biochemistry and endocrinology): a) Urine microalbumin, sodium, creatinine, free cortisol) b) TSH, FT4 c) 25 OH vitamin D	X							
Demographic details, questions on health status, lifestyle using MABAT questionnaire	X							
Functional and physical activity questionnaires	X							
Food frequency questionnaire	X							
Guidance about diabetes diary	X							
Drug guidance for drug arm only		X						
Dietary guidance for diet arm only			X	X	X		X	
CRT guidance for CRT arm only			X	X				
CRT guidance for drug and diet arms						X		
Height		X						
Body weight		X				X		X
Body circumferences		X				X		X
Body fat %, lean and muscle mass assessments using BIA method		X				X		X
Resting blood pressure		X				X		X
Resting energy expenditure		X				X		X
24 h blood pressure monitoring		X				X		X
Fasting plasma glucose and HbA1C		X				X		X
Testosterone (T) and bioavailable T		X				X		X
HOMA- Insulin X glucose/23.5		X				X		X
LH, FSH, Estradiol		X				X		X
Diabetes diary (self-monitoring glucose levels, change in drugs)		X				X		X

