##### Baseline comparisons

To test differences in continuous variables between the study groups the one-way analysis of variance (ANOVA) test will be performed (or Kruskal–Wallis one-way analysis of variance when normal distribution is rejected). For comparison of dichotomous or categorical variables the Chi square test will be performed.

The primary endpoints (% change in LBM and change in weight) will be analyzed using the analysis of covariance (ANCOVA) after 10 weeks and after 20 weeks (for diet and drug arms only) including several factors and covariates. Table 2 indicates the list of covariates and factors. Table 3 indicates the different outcomes and appropriate statistical method.

**Table 2 Tab2:** List of potential covariates and factors (partial list)

Factor or covariate	Type	Defined as
Treatment	Factor	SGLT2 inhibitor, diet, CRT
GLP1 agonists	Factor	Yes, no
Baseline body weight/ BMI	Covariate	–
HbA1c (%)	Covariate	–
Caloric consumption (Kcal)	Covariate	–
Resting metabolic rate (Kcal)	Covariate	–
Body fat %	Covariate	–
Strength (kg)	Covariate	–
Frailty or sarcopenia status	Factor	Frail or sarcopenic, pre-frail or pre sarcopenic and robust

*Abbreviations*: *BMI* Body Mass Index, *CRT* Circuit Resistance Training, *GLP-1* Glucagon-Like Peptide-1, *HbA1c* Hemoglobin A1C

**Table 3 Tab3:** The different outcomes and appropriate statistical method (partial list)

	Endpoint type	Statistical method
Primary outcome		
Change in body weight (%) from baseline to 10 weeks or to 20 weeks	Continuous	ANCOVA
Change in % lean body mass from baseline to 10 weeks or to 20 weeks	Continuous	ANCOVA
Proportion of participants having lost ≥2.5% at week 10 and 20	Binary	Logistic regression
Secondary outcomes		
Change in waist circumference from baseline to 10 weeks or to 20 weeks	Continuous	ANCOVA
Change in FPG and HB1Ac from baseline to 10 weeks or to 20 weeks	Continuous	ANCOVA
Change in sarcopenia and frailty status (improved vs. not improved; change from one level to the other) at week 10 and 20	Binary	Logistic regression
Change in strength and other functional abilities from baseline to 10 weeks or to 20 weeks	Continuous	ANCOVA
Change in systolic blood pressure from baseline to 10 weeks or to 20 weeks	Continuous	ANCOVA
Change in quality of life (improved vs. not improved; change from one level to the other) at week 10 and 20	Binary	Logistic regression

*Abbreviations*: *ANCOVA* Analysis of Covariance, *FPG* Fasting Plasma Glucose, *HbA1c* Hemoglobin A1C

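### The mixed model and the completer analysis require study completion, which means week 10 in the CRT arm but week 20 in the diet and drug arms

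*Protocol article*

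**What the plan says.** The arms differ in length. Under Follow up visits, the week-10 visit is given as "Week 10 (all arms; CRT arm – end of study" and the last visit as "Week 20 (SGLTT-2 and V-Med arms". Footnote c of Table 1 agrees: "At this week CRT group will finish the study and SGLTT-2 and V-Med add CRT on top of their current intervention". The primary endpoints are analysed "after 10 weeks and after 20 weeks (for diet and drug arms only", so week 10 is the only time at which all three arms can be compared.

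The text after Table 3 then describes the analysis sets:

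- The primary analysis is by intention to treat. Where the final examination is missing, the last available value is used, so completion is not required.
- The completer sensitivity analysis is "an analysis which includes only participants that fully completed the study (have an assessment at the end of study".
- The mixed model for repeated measurements, which the article says may be performed, is "based on assessments of participants who completed the study and had high compliance to the treatment".
- The per-protocol conditions are thresholds, for example "for participants who had high compliance to workout (≥ 2/3 of sessions" and "for participants who had high compliance to drug therapy (≥80% tablets taken". They carry no time window.

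Neither the completer set nor the mixed-model set has a separate week-10 version.

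**The concern.** Completion asks for 10 weeks of follow-up in one arm and 20 weeks, including acceptance of a second intervention, in the other two. If that single definition governs the week-10 comparison, membership in two arms depends on events after the outcome was measured, and membership in the third does not. Randomisation no longer protects such a comparison.

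The completer analysis is also the plan's own check on carrying the last observation forward. If it selects differently by arm, a disagreement with the primary result could come from the imputation or from the selection, and the two could not be told apart. The mixed model has a further loss: a repeated-measures model can use the week-10 value of someone who stops later, and the restriction discards it.

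**Working it through.** **Step 1. Who is in the set.** The timing statements, set against the literal definition of completion:

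| Arm | End of study | Week-10 data, stops in weeks 10-20 |
|---|---|---|
| CRT | week 10 | cannot occur |
| Diet | week 20 | excluded |
| Drug | week 20 | excluded |

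The mixed model is the clearer case. Table 1 schedules weight and body composition at baseline, week 10 and week 20. A repeated-measures model spans these visits with one membership rule per participant, so a person without week 20 also loses the week-10 value.

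**Step 2. Numbers retained.** The article gives attrition of about 10%, not split by arm or period. Assume a dropout fraction d in each 10-week period and 40 per arm (the planned size). Literal completers are 40(1 - d) in CRT and 40(1 - d)² in diet and in drug. The difference is the number with week-10 data who are removed.

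| d (assumed) | CRT | Diet or drug | Removed per arm |
|---|---|---|---|
| 5% | 38.0 | 36.1 | 1.9 |
| 10% | 36.0 | 32.4 | 3.6 |
| 20% | 32.0 | 25.6 | 6.4 |

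With a week-10 set, the expected number is the same in every arm: 38, 36 or 32.

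**Step 3. A standard deviation for scale.** The sample-size section gives a 3.2 kg difference, 80% power, 5% significance and 40 per arm, but no SD for weight. Solving the two-sided normal formula: SD = 3.2 / (1.960 + 0.842) × √(40/2) = 5.1 kg. With that SD, 40 per arm gives power 0.801, so the planned size is reproduced. The SD is implied, not stated.

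**Step 4. Possible shift of a week-10 mean.** Suppose a fraction q of those seen at week 10 is later removed, and the tendency to stay has correlation ρ with week-10 response. With c = Φ⁻¹(q), the retained mean shifts by ρ × SD × φ(c)/(1 - q). For q = 10%, φ(c)/(1 - q) = 0.195, so ρ = 0.3 gives 0.3 × 5.1 × 0.195 = 0.30 kg. Both q and ρ are assumptions.

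| q | ρ | Shift (kg) | Share of 3.2 kg | Simulated type I error |
|---|---|---|---|---|
| 10% | 0 | 0 | 0% | 0.049 |
| 10% | 0.3 | 0.30 | 9% | 0.056 |
| 10% | 0.5 | 0.50 | 16% | 0.062 |
| 20% | 0.3 | 0.54 | 17% | 0.074 |
| 20% | 0.5 | 0.89 | 28% | 0.106 |
| 30% | 0.5 | 1.27 | 40% | 0.156 |

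The last column is from a simulated nominal 5% t test of one selected arm against CRT: 36 per arm seen at week 10, no true difference, 4,000 runs. Its Monte Carlo standard error near 5% is √(0.05 × 0.95/4000) = 0.003, so 0.056 is hardly distinguishable from 5%. A negative ρ reverses the sign of the shift.

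**The case against.** The strongest reply is that the end of study may mean the end of the period being analysed. Under Definition of main outcomes, lean mass change is defined with the end-of-study value, yet Table 3 analyses that endpoint at both week 10 and week 20. On that reading the completer set at week 10 is simply everyone assessed at week 10. This partly stands: the completer wording is ambiguous. Against it, the adherence section sets the 10-week tablet count apart from the count at the end of the study, and Follow up visits uses the phrase for an arm's last visit. The reply does not rescue the mixed model, where one model covers both visits and requires study completion.

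A second reply is that an article leaves set membership by visit to the full protocol. That covers missing detail. It does not cover a restriction that the article itself states.

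A third is that little depends on these analyses. This stands as a limit on importance: the primary set is untouched, the mixed model is optional, and the trial is described as exploratory.

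A reader might also infer that the per-protocol set demands 20 weeks of completion and compliance. The text does not say so. It gives no completion rule and no window, and tablets and diet are assessed at week 10 and again at week 20 or the end of study. Likewise, the idea that someone who barely did the added CRT would count as compliant at week 20 requires reading the listed conditions as alternatives, which the text does not state.

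**Conclusion.** The concern holds for two supportive analyses: firmly for the mixed model, and on the literal reading for the completer analysis. Both can drop diet and drug participants from the week-10 comparison for events after week 10, with no counterpart in CRT. For the per-protocol set, the only fault is an unstated compliance window.

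The size is not known. The shifts of 0.30 to 1.27 kg (9% to 40% of the 3.2 kg design difference) rest on the implied SD of 5.1 kg and on assumed values of q and ρ. If later dropout is unrelated to week-10 response, there is no shift.

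It would be tempting to conclude that week 10 is biased in favour of diet and drug. The article does not support that: it gives nothing on who stops or why, and no direction can be shown for lean mass. The primary intention-to-treat set is not selected in this way. The wording should be corrected, but the main result does not depend on it.

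**What to change.** - **Mixed model:** include each participant's available visits and drop the requirement of study completion.
- **Completer set, week 10:** everyone in any arm with a week-10 assessment.
- **Completer set, week 20:** diet and drug participants with a week-20 assessment.
- **Per-protocol set:** judge compliance up to the time point analysed. For week 10, use the arm's own treatment over weeks 0-10. For week 20, use the arm's own treatment over weeks 0-20 together with the added CRT over weeks 10-20, with the thresholds already stated.

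This changes analysis wording only. Tablet counts and the diet score are already scheduled at weeks 10 and 20, and the CRT diary runs throughout, so no new data are needed. The cost is two set definitions instead of one.
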